## Abstract

**Background:**

Because type 2 diabetes mellitus is associated strongly with an increased risk of cardiovascular diseases, the number of patients with diabetes with chronic heart failure is increasing steadily. However, clinical evidence of therapeutic strategies in such patients is still lacking. A recent randomized, placebo-controlled trial in patients with type 2 diabetes with high cardiovascular risk demonstrated that the SGLT2 inhibitor, empagliflozin, reduced the incidence of hospitalization for heart failure. Because SGLT2 inhibitors cause a reduction in body weight and blood pressure in addition to improving glycemic control, they have the potential to exert beneficial effects on the clinical pathophysiology of heart failure. The aim of the ongoing CANDLE trial is to test the safety and non-inferiority of canagliflozin, another SGLT2 inhibitor, compared with glimepiride, a sulfonylurea agent, in patients with type 2 diabetes mellitus and chronic heart failure.

**Methods:**

A total of 250 patients with type 2 diabetes who are drug-naïve or taking any anti-diabetic agents and suffering from chronic heart failure with a New York Heart Association classification I to III will be randomized centrally into either canagliflozin or glimepiride groups (1: 1) using the dynamic allocation method stratified by age (<65, ≥65 year), HbA1c level (<6.5, ≥6.5 %), and left ventricular ejection fraction (<40, ≥40 %). After randomization, all the participants will be given the add-on study drug for 24 weeks in addition to their background therapy. The primary endpoint is the percentage change from baseline in NT-proBNP after 24 weeks of treatment. The key secondary endpoints after 24 weeks of treatment are the change from baseline in glycemic control, blood pressure, body weight, lipid profile, quality of life score related to heart failure, and cardiac and renal function.

**Discussion:**

The CANDLE trial is the first to assess the safety and non-inferiority of canagliflozin in comparison with glimepiride in patients with type 2 diabetes with chronic heart failure. This trial has the potential to evaluate the clinical safety and efficacy of canagliflozin on heart failure.

*Trial registration* Unique trial Number, UMIN000017669

**Electronic supplementary material:**

The online version of this article (doi:10.1186/s12933-016-0381-x) contains supplementary material, which is available to authorized users.

## Background

Co-morbidities associated with type 2 diabetes mellitus (T2DM) are increasing steadily in patients with chronic heart failure (CHF). Their prevalence was reported to be 30 % in the JCARE-CARD trial and 23 % in the CHART-2 trial [1, 2]. Complications of T2DM aggravate clinical outcomes, such as higher mortality, morbidity, and re-hospitalization rate for worsening heart failure in patients with CHF. This indicates that T2DM is a relatively strong risk factor for CHF [3, 4]. Although glycemic control is recognized as essential, a U-curve phenomenon is found between HbA1c levels and mortality in CHF patients with T2DM [5]. The treatment guidelines for CHF of the Japanese Circulation Society are similar to those of the American Heart Association and European Society of Cardiology in that the established evidence on the recommended therapeutic strategies in T2DM are not provided [6]. In addition, the Japan Diabetes Society has also not described specific treatment options for diabetes in patients with CHF, although lowering HbA1c levels to <7.0 % is recommended in order to suppress the development and progression of microvascular complications [7].

Sodium glucose co-transporter 2 (SGLT2) inhibitors are a novel class of anti-diabetic agents that have a blood glucose-lowering effect by increasing urinary glucose excretion [8, 9]. In addition to this glucose-lowering effect, previous studies have demonstrated that SGLT2 inhibitors decrease blood pressure (BP) due to their osmotic diuretic action, and also induce metabolic ameliorations, including a reduction of visceral fat and body weight (BW) [10–12]. The diuretic action of SGLT2 inhibitors may also have advantages on heart failure. Recently, it has been reported that administration of empagliflozin, a SGLT2 inhibitor, as an add-on to conventional anti-diabetic therapy, significantly reduced cardiovascular (CV) adverse outcomes in T2DM patients with higher CV risk [13]. Given their pleiotropic pharmacological actions, SGLT2 inhibitors appear to contribute to amelioration of the clinical course of T2DM patients with CHF by reducing both blood glucose and excess body fluid. Canagliflozin is another SGLT2 inhibitor and the first-in-class drug launched in the United States. In phase III clinical trials, canagliflozin was reported to cause favorable long-term glycemic and metabolic improvement and was well tolerated as either mono-therapy or in combination with other anti-diabetic agents [14–16]. Another randomized placebo-controlled trial designed to assess the longer-term effects of canagliflozin on clinical outcomes in T2DM patients is currently being carried out [17]. To enhance the favorable class effect of SGLT2 inhibitors on cardiovascular events, it is important to refer to additional trials on other SGLT2 inhibitors. However, T2DM patients with severe CHF with a New York Heart Association (NYHA) functional classification of III and IV were excluded from these trials, because the use of SGLT2 inhibitors is not clinically recommended in these patients. As a consequence, the clinical efficacy and safety of SGLT2 inhibitors in T2DM patients with CHF remains to be elucidated (Fig. 1).

**Fig. 1 Fig1:**
[figure not shown]
Trial concept. Conventional diuretics are well established agents for CHF. On the other hand, SGLT2 inhibitors are new anti-diabetic agents with multiple favorable effects such as improving glycemic and metabolic parameters. In addition, empagliflozin has recently been reported to reduce the risk of CV events *asterisk* [13]. However, the beneficial effects of SGLT2 inhibitors in T2DM patients with CHF have yet to be established. *BP* blood pressure, *BW* body weight, *CHF* chronic heart failure, *CV* cardiovascular, *SGLT2* sodium glucose cotransporter 2, *T2DM* type 2 diabetes mellitus

The CANDLE trial was designed to test the safety and non-inferiority of canagliflozin, compared with glimepiride, using N-terminal pro-brain natriuretic peptide (NT-proBNP) as the index of the therapeutic effects in T2DM patients with CHF. This trial has the potential to provide novel clinical evidence regarding the safety and efficacy of canagliflozin as anti-diabetic therapy in T2DM patients with CHF.

## Methods

### Study overview and design

The CANDLE trial is an ongoing, multicenter, prospective, randomized, open-label, blinded-endpoint investigator-initiated clinical trial. This study tests the hypothesis that additional administration of canagliflozin to standard therapy does not worsen the pathological state of CHF, compared to the conventional anti-diabetic agent, glimepiride. Twenty-four weeks after recruitment and randomization into either canagliflozin or glimepiride groups, the safety and non-inferiority of canagliflozin for T2DM patients with CHF will be evaluated using NT-proBNP as a biomarker of heart failure.

Prior to initiation, the study protocol needs to be approved by the local institutional review boards and independent ethics committees at every site. The trial will be conducted in full compliance with the Declaration of Helsinki and according to the Ethical Guidelines for Medical and Health Research Involving Human Subjects established by the Ministry of Health, Labour, and Welfare and Ministry of Education, Culture, Sports, Science, and Technology.

### Trial population and recruitment

We aim to recruit a total of 250 participants across approximately 35 sites in Japan. Recruitment for this trial began in October 2015 and will be completed by December 2017. Eligible patients in the trial are T2DM patients with CHF (aged ≥20 years) who comply with all the enrollment criteria. The detailed inclusion and exclusion criteria are listed in Table 1. Briefly these criteria include: (1) Patients with appropriately diagnosed T2DM, who are drug-naïve or taking any anti-diabetic agent; (2) T2DM clinically requiring a start or change of an anti-diabetic agent; (3) complicating NYHA functional classification I to III CHF, but not IV, with maintenance of the clinical condition and unchanged medical treatment for CHF, including angiotensin-converting enzyme inhibitors, angiotensin II receptor blockers, beta-blockers, and diuretic agents for 4 weeks prior to screening. In the trial, CHF is classified comprehensively by skilled cardiologists using several findings, including clinical symptoms (the Framingham criteria for congestive heart failure and NYHA functional classification), history of hospitalization for heart failure, and clinical tests such as echocardiography and biomarkers. However, there is no limitation on the NT-proBNP level at enrollment. Prior to eligibility screening, every participant is required to receive an adequate explanation based of the trial plan, with written informed consent then being obtained from each patient.

**Table 1 Tab1:** Detailed inclusion and exclusion criteria

Inclusion	Exclusion
Adults (aged ≥20 years)	Type 1 diabetes mellitus
T2DM patients who need to start or who are possibly changing or adding an anti-diabetic agent	History of diabetic ketoacidosis, diabetic coma, or hypoglycemic attack ≤6 months prior to informed consent
CHF (NYHA functional classification I to III)	Severe renal dysfunction (eGFR <45 ml/min/1.73 m^2^) or patients receiving dialysis
Without change in NYHA functional classification or drugs for heart failure 4 weeks prior to eligibility	Severe liver dysfunction (at least threefold higher AST or ALT more than the upper limit of the facilities reference value
The patient provided written informed consent to participate in the study	CHF (NYHA functional classification IV)
	Patients with pituitary or adrenal dysfunction
	Patients with malnutrition, starvation, irregular eating pattern, lack of dietary intake, or debilitation
	Patients with excess alcohol intake
	Patients in perioperative period around trial screening
	Patients with severe infection or trauma at trial screening
	Patients with a gastrointestinal disorder, such as diarrhea or vomiting
	Patients with low body weight (BMI **<**18.5 kg/m^2^)
	History of coronary artery disease, coronary vascularization, open-heart surgery, stroke, or transient ischemic attack ≤3 months prior to eligibility
	Patients with a malignancy
	History of hypersensitivity to ingredients of SGLT2 inhibitors or sulfonylureas
	Pregnant or suspected pregnancy in females
	Lactating female
	Considered inappropriate for the study by investigators due to other reasons

*ALT* alanine aminotransferase, *AST* aspartate transaminase, *BMI* body mass index, *CHF* chronic heart failure, *eGFR* estimated glomerular filtration rate, *NYHA* New York Heart Association, *SGLT2* sodium glucose cotransporter 2, *T2DM* type 2 diabetes mellitus

### Trial outline and follow-up

After informed consent has been provided and the eligibility assessment completed, all eligible participants will be randomized and assigned into either the canagliflozin or glimepiride groups. Post-randomized follow-up visits are scheduled at 4, 12, and 24 weeks (Fig. 2). All participants will see their usual-care physicians at each visit to receive usual-care and individualized appropriate treatment according to their background disease, T2DM, and CHF, in addition to administration of the study drug.

**Fig. 2 Fig2:**
[figure not shown]
Trial outline

### Randomization and treatment

Eligible patients with the appropriately signed informed consent will be randomized to either the canagliflozin or glimepiride groups at a ratio of 1:1 using the minimization method with biased coin assignment balancing for age (<65, ≥65 year), HbA1c level (<6.5, ≥6.5 %), and left ventricular ejection fraction (LVEF; <40, ≥40 %) at the time of screening [18, 19]. The trial is an open-label design, although the assessor(s) will be blinded to treatment randomization. The assessors will also be blinded to the primary end point, NT-proBNP level, by measurement at a central laboratory.

All participants receive the study drug for 24 weeks. Patients who are assigned to the canagliflozin group receive canagliflozin 100 mg once daily. The EMPA-REG OUTCOME trial reported small dose-dependent effects of empagliflozin (10 mg vs. 25 mg/day) on metabolic parameters. However, the two dose groups had similar hazard ratios for cardiovascular outcomes [13]. Some studies on canagliflozin showed that 100 mg/day had sufficient effects on metabolic parameters, while 300 mg/day was slightly more effective [14, 15, 20]. Importantly, only 100 mg/day is approved in Japan, and therefore the dose of canagliflozin is fixed at 100 mg/day in the canagliflozin group. Because of the possible risk of excess diuresis and subsequent dehydration by combined use of canagliflozin and diuretics, the dose of the diuretics may need to be reduced when necessary. Patients assigned to the glimepiride group are started at a dose of 0.5 or 1.0 mg once or twice daily. According to the individual’s glycemic control, the dose of glimepiride can be increased to 6.0 mg/day. For background therapy in both groups, participants who have been receiving any SGLT2 inhibitor other than canagliflozin need to discontinue it at the start of the washout period, for 4 weeks, prior to receiving the study drug, canagliflozin or glimepiride. While, participants who have been taking a sulfonylurea need to stop taking it in the canagliflozin group and need to change to glimepiride (if needed) in the glimepiride group at the initiation of the study drug (Additional file 1). Because of the possible risk of excess diuresis and subsequent dehydration by combined use of canagliflozin and diuretics, the dose of the diuretics may need to be reduced when necessary.

Although a specific numerical goal of HbA1c level is not set in this trial, all participants need to be treated to achieve a personalized goal recommended by the guidelines (details in Additional file 2) [7]. Drugs that must not be used in combination with the study drugs are listed in Table 2. Within the appropriate range of the therapeutic goal, the participant’s background treatment will be, in principle and if possible, unchanged during the trial interval. If participants cannot achieve their glycemic goal, co-administration of anti-diabetic agents other than SGLT2 inhibitors and sulfonylureas or increased dosages of the anti-diabetic agents other than the target agents in both groups may be initiated, with caution being taken to prevent the development of hypoglycemia. After the trial is completed, all participants can continue any anti-diabetic treatment in accordance with their individual condition.

**Table 2 Tab2:** Prohibited concomitant drugs

Canagliflozin group
SGLT2 inhibitors other than canagliflozin
Sulfonylureas
Pioglitazone
Glimepiride group
Sulfonylureas other than glimepiride
SGLT2 inhibitors
Pioglitazone

*SGLT2* sodium glucose cotransporter 2

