Of the various conventional anti-diabetic agents, thiazolidine derivatives are effective for improving insulin resistance by enhancing insulin sensitivity in peripheral tissues, but need to be administered with caution because of possible adverse effects such as worsening of edema and heart failure [39, 40]. Dipeptidyl peptitadase-4 inhibitors have been shown to have neutral effects on CV outcome in both the EXAMINE (alogliptin vs. placebo) and TECOS (sitagliptin vs. placebo) trials [41, 42]. However, the SAVOR-TIMI53 trial (saxagliptin vs. placebo) demonstrated recently a significantly higher incidence of hospitalization for heart failure in the saxagliptin group, compared to placebo [43]. Therefore, at present the clinical use of anti-diabetic agents in T2DM patients with CHF is, in part, somewhat limited. As a consequence, although these patients are considered to be at higher CV risk and require more effective treatment strategies to improve their clinical outcome, no specific treatment guidelines have been established. Metformin is recognized widely as the first line strategy for treatment of type 2 diabetes in the USA and Europe, with some study showing a preference for metformin over sulfonylureas in diabetes patients with heart failure [44, 45]. However, metformin is not necessarily a first line treatment option in Japan [7]. Although the present study excludes patients with renal dysfunction who are prohibited to receive metformin, metformin is contraindicated in Japan for patients with heart failure because of the risk of lactic acidosis. In addition, it has been reported that decreased insulin secretion capacity has a pivotal role in the development of T2DM in Japanese subjects and accordingly sulfonylureas are used more frequently than metformin in Japan [46]. To our knowledge, there is no direct evidence showing that sulfonylureas increase the risk of heart failure. A phase III trial in the USA showed sulfonylureas had similar power to decrease HbA1c levels as canagliflozin 100 mg/day [14]. We therefore selected glimepiride as the comparison agent.

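### Entry and rescue rules leave metformin open although the Discussion calls it contraindicated in heart failure, and the rescue exclusions do not match Table 2

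*Protocol article*

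**What the plan says.** Four places in the Protocol article bear on this point.

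- **Entry** (Methods, Trial population and recruitment, and Table 1). Patients are eligible "who are drug-naïve or taking any anti-diabetic agent". Chronic heart failure of NYHA class I to III is an inclusion criterion. Metformin use is not among the exclusions.
- **Prohibited drugs** (Methods, Randomization and treatment). "Drugs that must not be used in combination with the study drugs are listed in Table 2". For the canagliflozin group the table names other SGLT2 inhibitors, sulfonylureas and pioglitazone. For the glimepiride group it names other sulfonylureas, SGLT2 inhibitors and pioglitazone. Metformin appears in neither list.
- **Rescue** (same paragraph, after the reference to Table 2). Background treatment is to stay the same as far as possible, but if the glycaemic goal is not reached, "co-administration of anti-diabetic agents other than SGLT2 inhibitors and sulfonylureas or increased dosages of the anti-diabetic agents other than the target agents" may be initiated in both groups.
- **Discussion** (choice of comparator). "metformin is contraindicated in Japan for patients with heart failure because of the risk of lactic acidosis". The same paragraph says that thiazolidine derivatives "need to be administered with caution because of possible adverse effects such as worsening of edema and heart failure".

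**The concern.** The operative rules and the document's own safety statement point in different directions. A site that follows the entry criteria, Table 2 and the rescue sentence finds nothing against enrolling a metformin user, raising that patient's dose or adding metformin as rescue. A site that reads the Discussion finds the drug described as contraindicated in the condition that every participant must have. Two sites could therefore handle the same patient differently, each with support in the text. What is at stake is patient safety and consistent conduct between sites.

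A smaller drafting problem sits beside it. The rescue sentence carries its own exclusion list, and that list is shorter than Table 2. Two lists that serve the same purpose in one paragraph should agree.

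**Working it through.** The plan gives no figure on this point, so the check is a comparison of the text.

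**Step 1. Compare the lists agent by agent.**

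| Agent or class | Excluded by the rescue sentence? | Prohibited by Table 2? | Discussion |
|---|---|---|---|
| SGLT2 inhibitors | Yes | Yes, apart from canagliflozin in its own group | – |
| Sulfonylureas | Yes | Yes, apart from glimepiride in its own group | – |
| Pioglitazone | No | Yes, both groups | Class to be used with caution |
| Metformin | No | No | Contraindicated in heart failure in Japan |

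**Step 2. Metformin.** Three routes are open under the rules as written:

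- *Continued:* the entry wording admits patients on any agent, and neither Table 1 nor Table 2 removes metformin.
- *Started:* the first half of the rescue sentence allows added agents outside two named classes, and metformin belongs to neither.
- *Increased:* the second half allows higher doses of agents other than the study drugs, which includes metformin already in use.

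The Discussion statement applies to patients with heart failure. Table 1 requires heart failure, so the statement covers everyone enrolled. The sentence that contains it also refers to this trial's exclusion of patients with renal dysfunction before it states the contraindication, so it was written with this population in view. Nothing in the shown text makes the statement compatible with the three routes.

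**Step 3. Pioglitazone.** Taken alone, the rescue sentence does not exclude it. The prohibition that introduces Table 2 stands earlier in the same paragraph, is unconditional and has no exception for rescue. The rescue sentence does not lift it. Read together, the two statements bar pioglitazone in both groups. What is left is a mismatch: the rescue sentence repeats two of Table 2's three entries and omits the third.

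**The case against.** The strongest case against the point is that a national contraindication binds prescribers whether or not a trial table repeats it. The metformin remark is Discussion text that explains the choice of comparator and is not an operative rule. The article also requires treatment towards guideline-based individual goals. Additional files 1 and 2, cited for background therapy and glycaemic goals, are not shown and may say more.

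Much of this stands, and it keeps the point minor. It does not remove the inconsistency. The Discussion asks only for caution with the thiazolidine class, and Table 2 nevertheless prohibits pioglitazone. For metformin the Discussion uses the stronger word, and Table 2 is silent. A site could reasonably take a table of prohibited drugs as complete.

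A reader might infer more than the text supports:

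- *That pioglitazone rescue is allowed.* Table 2 prohibits it without condition.
- *That rescue would distort NT-proBNP by a calculable amount.* The only class the document links to oedema is the thiazolidine derivatives, and pioglitazone, the one member it names, is barred. No statement says that metformin changes NT-proBNP.
- *That saxagliptin is a second contradiction.* The Discussion reports a trial that "demonstrated recently a significantly higher incidence of hospitalization for heart failure in the saxagliptin group", but never calls the drug contraindicated or excluded here, so its absence from Table 2 conflicts with nothing.
- *That lactic acidosis would go unrecorded because the Safety section does not list it.* The safety endpoints cover adverse effects and drug reactions in general.

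**Conclusion.** The point holds as a minor inconsistency with two parts. First, the entry wording, the rescue sentence and Table 2 together leave metformin open, while the Discussion calls it contraindicated in the population under study. Second, the exclusion list in the rescue sentence is shorter than Table 2.

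Its size cannot be put in numbers. The statement about heart failure covers all participants, but the practical consequence is confined to those who take or are given metformin, and the document gives no count or expected share of them. The conclusion assumes that the additional files, which are not shown, do not already settle the matter. It makes no claim about bias in the primary comparison, and it does not say which of the conflicting clinical statements is right.

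**What to change.** The sponsor should reconcile four pieces of text: the eligibility wording on prior anti-diabetic agents, the rescue sentence, Table 2 and the Discussion statement on metformin. The rescue sentence and Table 2 should be made to agree. The sponsor's clinicians decide the content. If an additional file already covers metformin, a reference to it at these places would do.

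The cost is a short amendment and a notice to sites. Depending on how the passages are reconciled, there may be fewer rescue options, or metformin users may need review at entry. The sample size and the planned analysis do not change.
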